## Abstract

**Background:**

With 30%–50% of people with bipolar depression (BDep) not responding to multiple pharmacological treatments, alternative therapies are needed. Accelerated intermittent theta burst stimulation (aiTBS) over the left dorsolateral prefrontal cortex (L‐DLPFC) has been employed for individuals with pharmacological treatment‐resistant major depressive disorder (TR‐MDD). Imaging studies have revealed reduced regional activity of the L‐DLPFC for both TR‐MDD and pharmacological treatment‐resistant BDep (TR‐BDep), suggesting that aiTBS over the L‐DLPFC may be beneficial for people with TR‐BDep.

**Methods:**

A 6‐week, double‐blind, sham‐controlled, randomized trial will be conducted to compare the efficacy and safety of aiTBS to the L‐DLPFC in people with TR‐BDep (jRCTs042240019). Fifty iTBS sessions (1800 pulses/session) will be delivered in 10 daily sessions over 5 consecutive days at 90% resting motor threshold. This aiTBS protocol is termed as Fujita Neuromodulation Therapy for Bipolar Depression (FNT‐BD). Twenty‐two participants (both sexes, aged 18–64 years) with TR‐BDep (DSM‐5‐TR, Type I) will be recruited. The response rate at any given week of follow‐up will be the primary efficacy outcome, defined as a reduction of ≥50% in the Montgomery Åsberg Depression Rating Scale (MADRS) score. Other outcomes will include MADRS score changes, remission rate (10 ≥ MADRS score), Clinical Global Impression‐Improvement score, Clinical Global Impression‐Severity score, discontinuation rate, and incidence of individual adverse events.

**Results:**

We anticipate that individuals who receive the aiTBS treatment show significant improvement in depressing symptoms compared to those receiving sham treatment.

**Conclusions:**

This study will provide valuable evidence for both patients with TR‐BDep and clinicians.

## INTRODUCTION

Bipolar disorder (BD) is a common and serious mental illness that affects approximately 1% of the population.^1^, ^2^ Individuals with BD frequently exhibit mania/hypomania or depression, which can cause social and occupational disability.^2^ A review of suicide cases in people with BD demonstrated that the risk of suicide is 20–30‐fold higher than in the general population.^3^ According to the *Diagnostic and Statistical Manual of Mental Disorders*, Fifth Edition, Text Revision (DSM‐5‐TR),^4^ bipolar I disorder can be established with the occurrence of a manic episode alone; however, the diagnosis of bipolar II disorder requires at least one distinct episode of hypomania and one distinct episode of major depression.

For both the acute and maintenance phases, including mania and depression, the primary treatment is pharmacological treatment using mood stabilizers (MSs) and second‐generation antipsychotics (SGAs).^2^, ^5^, ^6^ A recent network meta‐analysis found that olanzapine plus fluoxetine, quetiapine, olanzapine, lurasidone, lumateperone, cariprazine, and lamotrigine were more effective than placebo in reducing depressive symptoms, with moderate confidence in the evidence.^7^ However, 30%–50% of individuals with bipolar depression (BDep) fail to respond to multiple pharmacological treatments.^8^, ^9^, ^10^, ^11^ Thus, a novel treatment for these people is warranted.

Recently, repetitive transcranial magnetic stimulation (rTMS) has gained worldwide attention as a treatment option for various neurological and psychiatric conditions. The US Food and Drug Administration approved rTMS, a noninvasive therapeutic brain‐stimulation technique, for modulating the regional excitability of the human brain for pharmacological treatment‐resistant major depressive disorder (TR‐MDD), obsessive–compulsive disorder, and smoking cessation.^12^ rTMS directed at the left‐dorsolateral prefrontal cortex (L‐DLPFC) increases L‐DLPFC activity, which is underactive in patients with TR‐MDD and enhances therapeutic connections with the anterior cingulate and amygdala, both of which play vital roles in coordinating stress responses.^13^, ^14^, ^15^ Intermittent theta burst stimulation (iTBS) over the L‐DLPFC (iTBS [L‐DLPFC]) is a novel noninvasive therapeutic brain‐stimulation technique for TR‐MDD.^12^ Generally, iTBS is delivered more rapidly than traditional high‐frequency rTMS (HF‐rTMS).^16^, ^17^ A recent randomized controlled trial (RCT) elucidated that iTBS (L‐DLPFC) provided comparable effects on TR‐MDD to HF‐rTMS over the L‐DLPFC (HF‐rTMS [L‐DLPFC]),^18^ suggesting that iTBS (L‐DLPFC) may be a more practical and potentially more effective therapeutic modality. Our previous pairwise meta‐analysis also showed that iTBS (L‐DLPFC) and HF‐rTMS (L‐DLPFC) show no significant differences in efficacy, acceptability, and safety profiles.^17^

In both people with TR‐MDD and those with pharmacological treatment‐resistant BDep (TR‐BDep), imaging studies demonstrated a reduction in the regional activity of the L‐DLPFC.^19^, ^20^ Evidence also suggests that electroconvulsive therapy, another neuromodulation treatment, is effective for both TR‐MDD and TR‐BDep.^21^ In fact, our meta‐analysis indicated that rTMS was effective for both TR‐MDD and TR‐BDep.^22^ Furthermore, our meta‐regression analysis demonstrated no significant differences in the magnitude of the antidepressant effect of iTBS (L‐DLPFC) between people with TR‐MDD and those with TR‐BDep.^22^ However, the effect sizes of the current iTBS (L‐DLPFC) protocols on people with TR‐BDep were small.^22^ Recently, accelerated intermittent theta burst stimulation (aiTBS) over the L‐DLPFC (aiTBS [L‐DLPFC]), also known as Stanford Neuromodulation Therapy (SNT), has been demonstrated to be more effective for people with TR‐MDD.^23^ SNT utilizes resting‐state functional connectivity magnetic resonance imaging (MRI) to individually identify and target the region of the L‐DLPFC that is most anticorrelated with the subgenual anterior cingulate cortex in each participant.^23^ This protocol comprises 10 iTBS (L‐DLPFC) sessions that are delivered daily, for a total of 18,000 pulses per day on 5 consecutive days.^23^ An RCT of SNT found that the aiTBS (L‐DLPFC) outperformed sham in improving depressive symptoms, with a large effect size (Cohen's *d* > 0.8).^24^ We propose that developing an aiTBS (L‐DLPFC) protocol, such as SNT, for people with TR‐BDep is necessary.

## METHODS

### Study design

A 6‐week, double‐blind, sham‐controlled, randomized trial to compare the efficacy and safety of aiTBS (L‐DLPFC) in people with TR‐BDep will be conducted. The study has been registered with Japan Registry for Clinical Trials (jRCT) under the identifier jRCTs042240019. The study has been ongoing at the Fujita Health University Hospital (Toyoake) since September 2024 and for completion on March 31, 2027.

### Participants

Beginning in September 2024, a total of 22 eligible participants (males and females aged 18–64 years) will be recruited from outpatients or inpatients with TR‐BDep at Fujita Health University Hospital. A recent review reported that cognitive dysfunction occurs frequently in elderly adults with BD.^25^ A higher dementia prevalence is found in BD compared with healthy peers and other psychiatric populations.^25^ Therefore, our study will exclude elderly adults with BD. Every potential participant who consents will be invited to participate in the study. Full inclusion and exclusion criteria are summarized in Table 1.

**Table 1 pcn570064-tbl-0001:** Inclusion and exclusion criteria.

*Inclusion criteria*
1. Individuals will be given a detailed description of the clinical trial, and all participants and their guardians will provide written informed consent. 2. Age: ≥18 years old and <65 years old at baseline 3. People who will meet the DSM‐5‐TR criteria for bipolar depression (Type I) 4. Individuals who will be diagnosed with pharmacological treatment‐resistant^a^ bipolar depression 5. People who will have a HAM‐D17 total score of 20 or higher at baseline
*Exclusion criteria*
1. Individuals with metal implants or devices near the stimulation site (e.g., cochlear implants, surgical clips with magnetic properties, or neurostimulators, such as deep brain stimulation or vagus nerve stimulation), individuals with a cardiac pacemaker 2. Individuals with metal implants or devices that are not near the stimulation site (e.g., implanted medication pumps), titanium products in their heads, magnetic dentures/implants 3. Individuals with a history of seizures, a history of intracranial lesions at risk of seizures, individuals taking drugs that reduce seizure threshold (methylphenidate or ketamine), individuals with alcohol/caffeine/stimulants abuse or withdrawal symptoms, pregnant individuals, and individuals with severe physical disease 4. Individuals who have received rTMS during their current depressive episode 5. Persons diagnosed with dementia, organic or symptomatic mood disorder 6. Individuals with unimproved depressive symptoms due to inadequate adherence to pharmacological treatment 7. Individuals diagnosed with substance‐related or medication‐induced mood disorders 8. Individuals who will answer “yes” to Question 1 (Do you have the intention to carry out a suicidal act, although you do not have a specific plan to do so?) or Question 2 (Do you have a specific plan and intention to carry out a suicidal act?) at baseline^b^ 9. Individuals deemed inappropriate by researchers

^a^
The definition is that an individual who will not respond to at least two mood stabilizers or second‐generation antipsychotics (valproate, lamotrigine, quetiapine extended‐release, lurasidone, or olanzapine that have been reported to have efficacy for bipolar depression by a network meta‐analysis^7^) with a sufficient dose (within the doses approved in Japan [PMDA]) for 2 weeks or more (CGI‐S score ≥4, we will confirm the result from their medical records). If the patients are receiving combination therapy with two or more of these drugs, we will choose the candidate drug with the highest DDD‐equivalent value among the drugs. If two or more drugs used the same DDD‐equivalent value during the same period, we will select one of these drugs to evaluate the definition.

DDD: https://www.who.int/tools/atc-ddd-toolkit/about-ddd

PMDA: https://www.pmda.go.jp/english/index.html

^b^
The questions referred to the Columbia‐Suicide Severity Rating Scale.^26^

Abbreviations: CGI‐S, Clinical Global Impression‐Severity Scale; DDD, defined daily dose; DSM‐5‐TR, *Diagnostic and Statistical Manual of Mental Disorders*‐Fifth Edition‐Text Revision; HAM‐D17, 17‐item Hamilton Rating Scale for Depression; PMDA, Pharmaceuticals and Medical Devices Agency; rTMS: repetitive transcranial magnetic stimulation.

TR‐BDep is defined as an individual who will not respond to at least two MSs or SGAs (valproate, lamotrigine, quetiapine extended‐release, lurasidone, or olanzapine that are reported to have efficacy for BDep by a network meta‐analysis^7^) with a sufficient dose (within the doses approved in Japan^27^) for 2 weeks or more (Clinical Global Impression‐Severity [CGI‐S]^28^ score ≥4, we will validate the result from their medical records). If patients are receiving combination therapy with two or more of these drugs, we will select the candidate drug with the highest defined daily dose (DDD),^29^ with an equivalent value among the drugs. If two or more drugs used the same DDD‐equivalent value during the same period, we will use one of them to evaluate the definition. Lithium is one of the key drugs for the treatment of BD^6^; however, recent network meta‐analysis showed that lithium did not improve depressive symptoms in people with BDep.^7^ Therefore, we did not include lithium as a candidate drug for nonresponse. Several diagnostic tests showed that patients who did not show minimal improvement by Week 2 of pharmacological treatment were unlikely to respond later and might benefit from a treatment change.^30^, ^31^ Therefore, the observation period for drug treatment response was set to a minimum of 2 weeks. Antipsychotics, MSs, antidepressants, anxiolytics, and/or sleeping pills will be permitted with doses maintained constantly throughout the period of randomized treatment.

### Primary and secondary outcome measures

The response rate at any given week of follow‐up is the primary efficacy outcome. The response will be defined as a reduction of ≥50% in the Montgomery Åsberg Depression Rating Scale (MADRS)^32^ score. Secondary efficacy outcomes include response rate at 5–7 days, Week 2, 4, and 6; changes in the MADRS score at 5–7 days, Week 2, 4, and 6; remission rate (10 ≥ MADRS score) at 5–7 days, Week 2, 4, and 6; Clinical Global Impression‐Improvement^28^ score at 5–7 days, Week 2, 4, and 6; CGI‐S for mania^28^ score at 5–7 days, Week 2, 4, and 6; and CGI‐S for depression^28^ score at 5–7 days, Week 2, 4, and 6. The definitions of “response” and “remission” in our study are the same as that of the SNT study.^23^, ^24^ Table 2 illustrates the schedule of these psychometric assessments. Other outcomes include the discontinuation rate and the incidence of individual adverse events.

**Table 2 pcn570064-tbl-0002:** The SPIRIT schedule of these psychometric assessments.

	At baseline	Days 5–6	Week 2	Week 4	Week 6	When dropping out
MADRS	✔	✔	✔	✔	✔	✔
CGI‐S	✔	✔	✔	✔	✔	✔
CGI‐I		✔	✔	✔	✔	✔

Abbreviations: CGI‐I, Clinical Global Impression‐Improvement Scale; CGI‐S, Clinical Global Impression‐Severity Scale; MADRS, Montgomery Åsberg Depression Rating Scale.

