### Statistical analysis

Descriptive statistics will be computed for all variables of interest. Continuous measures, like age, will be summarized using means and standard deviations, while categorical measures will be summarized with counts and percentages. The data will be analyzed on a full analysis set, with endpoint analysis using the last‐observation‐carried forward method. The full analysis set will include all patients who agree to provide a baseline and at least one postbaseline data measurement. Response and remission rates will be evaluated using a *χ*
^2^ test. In Week 6, the MADRS score will be calculated using generalized linear mixed models. All statistical tests will be two‐sided, with significance defined as *p* < 0.05.

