We acknowledge funding from the Japan Agency for Medical Research and Development (24dk0307129h0001). The funding source will play no role in the study's design and execution, data collection, management, analysis, interpretation, manuscript preparation, review, approval, or decision to submit the manuscript for publication. For each visit, participants in this study will receive a monetary compensation of 10,000 Japanese yen. The study data will be collected and managed using REDCap electronic data capture tools hosted at Fujita Health University School of Medicine.^37^, ^38^ REDCap is a secure, web‐based software platform designed to support data capture for research studies. It includes (1) an intuitive interface for validated data capture; (2) audit trails for tracking data manipulation and export procedures; (3) automated export procedures for seamless data downloads to common statistical packages; and (4) data integration and interoperability procedures with external sources. Access to study data in REDCap will be restricted to study team members who have authenticated using Fujita Health University credentials.

Data is handled, computerized, and stored in accordance with the Clinical Trials Act of 2017. Paper copies of trial‐related documentation are annotated, signed, and dated before being filed in the electronic medical records. The Principal Investigator is responsible for the overall quality and retention of trial data. All trial data are retained following the most recent Directive on GCP (2005/28/EC) and local policy.

Staff collect clinical and safety data for trial participants, which are then recorded in the electronic case report form (eCRF) of the clinical data management system REDCap and password‐protected trial spreadsheets. The eCRFs and trial spreadsheets utilize unique trial identifier numbers to identify participants. A Data Monitoring Committee evaluates patient safety in a clinical trial of an investigational intervention through periodic review of adverse events and clinical safety assessments. Posttrial care of the study participants is ensured by the possibility of further treatment in the standard care setting.

Study results will be disseminated through publication in international peer‐reviewed journals and conference presentations to mental health professionals.

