## DISCUSSION

A recent network meta‐analysis elucidated that olanzapine plus fluoxetine, quetiapine, olanzapine, lurasidone, lumateperone, cariprazine, and lamotrigine were more effective than placebo at reducing depressive symptoms,^7^ although 30%–50% of individuals with BDep are refractory to pharmacological treatments.^8^, ^9^, ^10^, ^11^ Thus, we believe that developing a novel treatment for these people is warranted. The proposed study will be the first to use an RCT to explore the effects of a high‐dose iTBS (L‐DLPFC) protocol on TR‐BDep. We anticipate that people receiving our aiTBS (L‐DLPFC) treatment will experience significant improvements in depressive symptoms compared to those receiving sham treatment. According to the SNT study, the aiTBS (L‐DLPFC) protocol was well tolerated by the participants.^24^ This study will provide important evidence for TR‐BDep patients and clinicians.

Our study protocol has several limitations. First, the period during which response to the drug is evaluated may be short (minimum 2 weeks). Second, our study allows the use of concomitant medications. Because benzodiazepine administration may inhibit rTMS response, whereas psychostimulant use may be associated with a greater rTMS response,^39^, ^40^ the medications might influence the study results. Third, the SNT study is often stimulated at approximately 110% of the RMT after correction.^23^, ^24^ Because the protocol in our study does not use individual navigation for each participant, depth correction might be difficult to implement, raising concerns that the stimulation intensity may be low. Fourth, the range of interval session in our study is 30–50 min, and the factor might be a confounding factor. We will report an association between factors that will be included in the statistical analysis as a variable and the results of our study in the next paper.

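### In an all-bipolar I trial, CGI-S for mania is classed as a secondary efficacy score by visit; it would serve better as a safety outcome, shown per patient as worst value against baseline (minor)

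*Protocol article*

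**What the plan says.** The Study design section gives the comparison of efficacy and safety as the aim. Table 1 admits only Type I bipolar depression with a HAM-D17 total of at least 20. Its exclusion criteria do not mention manic or mixed symptoms at entry.

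In Primary and secondary outcome measures, one list opens with "Secondary efficacy outcomes include response rate at 5–7 days, Week 2, 4, and 6". The same list contains "CGI‐S for mania^28^ score at 5–7 days, Week 2, 4, and 6", next to the corresponding depression score. A separate sentence covers the safety-type outcomes: "Other outcomes include the discontinuation rate and the incidence of individual adverse events". No manic switch outcome, cut-off or worst-value summary is given, and no second mania scale is named.

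Table 2 schedules CGI-S at baseline, at four post-baseline visits and at drop-out. It has a single CGI-S row and does not separate mania from depression. In Ethics and dissemination, a Data Monitoring Committee evaluates patient safety "through periodic review of adverse events and clinical safety assessments".

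**The concern.** A secondary efficacy outcome is read for benefit. Patients who enter depressed probably have little mania to lose, so this score has little room to improve. What it can mainly show is a rise after treatment starts. Grouped with efficacy, the one mania-specific rating stands apart from the adverse events with which it should be read.

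The form of the outcome matters too. The clinical question is how many patients became more manic at any time. A summary at each visit answers a different question, namely how the group stood on that occasion. Brief rises in different patients at different visits are then divided among several summaries, each of which looks small. At stake is how clearly the trial can report on mania. The efficacy conclusion is not affected.

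**Working it through.** **Inputs.** 11 per arm, 22 in total, response rates of 85.7% and 26.7%, and about 7% drop-out (Sample size calculation); four post-baseline visits (outcome section and Table 2). The article gives no mania scores and no switch rate, so those used below are assumptions.

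**1. The plan's own figure.** The only stated figure used here is 11 per arm. For two proportions, two-sided 0.05, 80% power, no continuity correction:

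n = [1.96·√(2 × 0.562 × 0.438) + 0.842·√(0.857 × 0.143 + 0.267 × 0.733)]² / 0.59² = (1.375 + 0.475)² / 0.348 = 9.8, so 10 per arm.

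With 7% drop-out, 10 / 0.93 = 10.8, so 11. The figure reproduces, and nothing proposed here changes it.

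**2. Visit summaries against worst value.** Assume 11 patients, all with baseline score 1. Three of them each reach 5 once, at three different visits, and are otherwise at 1.
- Mean at each of those three visits: (10 × 1 + 5) / 11 = 1.36. Mean at the remaining visit: 1.00.
- Mean worst value: (8 × 1 + 3 × 5) / 11 = 2.09.
- Patients with a rise from baseline by worst value: 3/11 = 27%.

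Each visit shows a mean shift of 0.36, while the per-patient view shows that over a quarter of the arm had a marked rise. The by-visit data still contain all three rises; the summary dilutes them.

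**3. What 11 per arm can say.** These figures describe the sample size. They are the same whichever label the score carries and do not measure the defect.
- No switches in 11: exact 95% upper limit 1 − 0.025^(1/11) = 28.5%.
- One in 11: 9.1%, exact interval 0.2% to 41.3%.
- Expected drop-out is 22 × 0.07 = 1.54 patients. If one patient in an arm had no rating, 0/10 would give 1 − 0.025^(1/10) = 30.8%.
- Chance that an arm of 11 shows no switch, (1 − p)^11: 57% for p = 5%, 31% for p = 10%, 9% for p = 20%.
- Two-sided Fisher test of k/11 against 0/11, p = 2·C(11,k)/C(22,k): 0.21 for k = 3, 0.090 for k = 4, 0.035 for k = 5.

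Five switches against none would be needed to reach p < 0.05, so the display should be descriptive.

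**The case against.** The strongest objection is that only the efficacy label is fixed in the article. How the score is displayed may be set in an analysis plan that is not shown, and grouping it with the other psychometric ratings is an understandable arrangement. This stands, and it keeps the point small. The label and the by-visit form are nevertheless stated, and both can be improved.

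A worst value has its own weakness: it depends on how often a patient is rated. A completer has four scheduled chances to show a rise and an early leaver may have one or two, so unequal drop-out would distort the comparison between arms. This stands too, and the proposal has to allow for it. Small rises are also not switches.

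A reader might infer four stronger points that the documents do not support.
- *Mania would go unseen.* Switches may be captured as individual adverse events, and nothing keeps the rating from the Data Monitoring Committee.
- *The general rule, "with endpoint analysis using the last‐observation‐carried forward method", hides early rises.* The outcome list keeps all four visits, so a Week 2 rise still appears at Week 2.
- *The full analysis set drops the patients who matter.* A patient without a post-baseline rating has no worst value in any analysis set, and Table 2 schedules a rating at drop-out.
- *This rating is the only systematic evidence on mania.* The Discussion does rest its tolerability statement on the SNT study ("According to the SNT study, the aiTBS (L‐DLPFC) protocol was well tolerated by the participants"), which the Introduction presents in major depression. But the Intervention section also cites an earlier accelerated iTBS study in treatment-resistant bipolar depression, and the Introduction cites a meta-analysis covering rTMS in that condition. The article does not show what either found on mania.

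**Conclusion.** The point holds as a minor, inexpensive improvement. A score that mainly records harm is classed as efficacy and specified only by visit, in a trial that has safety as an aim and enrols only bipolar I patients. No figure is wrong, and the primary analysis, sample size, power and alpha are untouched.

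Two assumptions carry the conclusion. The first is that mania scores are mostly low at entry. This is likely in patients selected for depression but not guaranteed, because manic symptoms are not excluded; hence the comparison with each patient's own baseline. The second is that the single CGI-S row in Table 2 covers the mania rating at baseline and at drop-out. The size of the dilution in the illustration depends on assumed scores and is not an estimate for this trial.

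**What to change.** Before unblinding, move CGI-S for mania from the secondary efficacy outcomes to safety. Keep the by-visit scores as description. Beside the adverse-event table, add one descriptive table by arm with:
- each patient's baseline value, worst post-baseline value (including the drop-out rating) and number of post-baseline ratings;
- the number of patients with a rise from baseline or a mania or hypomania adverse event, with an exact 95% interval per arm and no formal test.

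If a cut-off is wanted for the rise, fix it before unblinding and justify it for mania. Confirm in Table 2 that the mania rating is made at baseline and at drop-out. The same table can go to the Data Monitoring Committee.

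The cost is a change of wording and one table. If Table 2 covers the mania rating as assumed, no new visit or procedure is needed. The remaining drawbacks are imprecise counts, small rises counted together with real switches (which is why individual values are shown), and the dependence of a worst value on the number of ratings (which is why that number is shown).
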